## Abstract

**Background/Objectives:** Permanent colostomy requires significant physical and psychological adaptation. Patients often experience reduced physical activity, impaired quality of life, and fear of movement. Current exercise recommendations are inconsistent, and no consensus exists on safe return to activity. This study aims to evaluate the effect of a 12-week home-based graded exercise programme on physical activity, quality of life, kinesiophobia, exercise capacity, and self-efficacy in patients with permanent colostomies. **Methods:** This randomized controlled trial will recruit 51 adults with permanent colostomies, beginning six weeks post-surgery. Participants will be randomized (1:1) to an intervention or control group. The intervention group will receive a 12-week home-based exercise programme including patient education, resistance and core training, and progressive aerobic walking. The control group will receive standard medical care and an informational leaflet. Primary outcomes include physical activity (steps/day), quality of life (Stoma-QoL), kinesiophobia (Tampa Scale), exercise capacity (6-Minute Walk Test), and self-efficacy (General Self-Efficacy Questionnaire). Follow-up will be conducted at baseline, post-intervention, and six months. Data will be analyzed using intention-to-treat principles with a significance threshold of *p* < 0.05. **Conclusions:** This trial will be the first to assess the effects of a structured, home-based graded exercise programme in individuals with permanent colostomies. The findings are expected to provide evidence on the efficacy of exercise for improving physical and psychological outcomes in this population and to inform clinical guidelines for safe, individualized activity resumption.

## 1. Introduction

A colostomy is a surgical procedure performed to divert intestinal transit when anatomical or functional abnormalities prevent normal fecal evacuation through the anal canal. It creates an opening in the abdominal wall through which waste is expelled into an external pouch [1,2].

Colostomies represent a primary therapeutic option for conditions such as colorectal cancer, diverticulitis, severe trauma, inflammatory bowel diseases, and congenital disorders. Depending on the underlying cause, colostomies may be temporary or permanent. Permanent colostomies, in particular, require substantial adaptation, as they affect gastrointestinal function, body image and daily activities [3].

In the United States, it is estimated that nearly one million individuals currently live with an ostomy, with 100,000 to 130,000 new procedures performed each year [4]. Across the European Union, it is estimated that 725,000 to 1 million individuals live with an ostomy, a figure expected to rise in parallel with the increasing prevalence of inflammatory bowel disease and other gastrointestinal disorders [5]. This condition may lead to complications that adversely affect quality of life, often resulting in physical, psychological and social challenges [4,6,7,8,9,10].

Stoma-related issues, such as bleeding, necrosis, prolapse and hernias, are common and frequently accompanied by sexual dysfunction, fatigue and bowel irregularities [1,11,12,13]. These impairments are closely linked to psychological distress, including depression, anxiety [14], disturbances in body image [15] and decreased physical activity [16,17].

Russell et al. investigated the attitudes and perceptions of 2631 ostomy patients regarding exercise, reporting a prevalent fear of physical activity, low activity levels, limited knowledge, and the perception of parastomal hernia risk as a major barrier to participation in exercise programmes [17]. Interventions in this population have primarily targeted hernia prevention [18], improvements in quality of life [19,20,21,22,23], pain reduction, and mental health support [22,24,25]. However, there is currently no consensus regarding the safe resumption of physical activity following colostomy, highlighting the need for gradual, individualized exercise programmes that educate patients and promote safe and progressive activity.

The selection of study variables was based on the multifactorial nature of adaptation following colostomy. Physical activity was included as a primary indicator of behavioural change and global recovery, since reduced activity levels have been consistently linked to postoperative complications and poorer health outcomes [26,27,28]. Quality of life represents a central construct integrating physical, psychological, and social dimensions, which are often impaired in this population. Kinesiophobia, or fear of movement, was incorporated because it constitutes a psychological barrier to physical rehabilitation and has been associated with decreased participation and delayed functional recovery in various clinical populations [29,30]. Exercise capacity, measured through the Six-Minute Walk Test, provides an objective index of functional performance and tolerance to physical effort [31]. Finally, self-efficacy was selected as it reflects patients’ confidence in managing their condition and performing physical activity safely, a critical determinant of adherence and long-term lifestyle modification [32]. Together, these outcomes provide a comprehensive assessment of both physical and psychological domains relevant to recovery after permanent colostomy.

Given the heterogeneity of exercise recommendations for permanent colostomy patients, personalized home-based programmes are required to reduce barriers and improve adherence. The present study aims to evaluate the effect of a home-based gradual exercise programme on physical activity, quality of life, kinesiophobia, exercise capacity, and self-efficacy in individuals with permanent colostomies. A six-month follow-up will also be conducted to assess patient adherence and programme satisfaction. We hypothesize that participants who complete the 12-week home-based gradual exercise programme will demonstrate greater improvements in physical activity levels, quality of life, kinesiophobia, exercise capacity, and self-efficacy compared with those receiving standard medical care.

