#### 2.6.2. Control Group

The control group will receive standard medical care and an informational leaflet covering colostomy management and common barriers to physical activity. No supervised exercise intervention will be provided.

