### 2.9. Statistical Analysis

Data will be analyzed using the Statistical Package for the Social Sciences (SPSS) for Windows (version 26; IBM, Armonk, NY, USA). Categorical data will be expressed as frequency (percentage). Continuous variables will be presented as mean ± standard deviation (SD). The normality of the data will be tested using the Shapiro–Wilk test. Effect sizes will be reported using partial eta-squared (η^2^) and interpreted according to standard conventions.

To evaluate the effects of the intervention over time, a Mixed ANOVA with a Group (intervention vs. control) × Time (baseline, post-intervention, 6 months) interaction will be conducted for all primary outcomes. Post hoc comparisons with Bonferroni correction will be performed if significant interactions are found. Secondary analyses will include intention-to-treat and per-protocol approaches as described above. Statistical significance will be established at *p* < 0.05.

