Self-efficacy is a widely studied variable in patients living with a permanent colostomy [68]. Previous studies have reported a direct association between self-efficacy and self-esteem [89]. Social support has also been identified as a key determinant of higher self-efficacy [90,91]. Lower levels of self-efficacy following surgery have been linked to more long-term psychosocial difficulties and worse adaptation to life with a colostomy [92]. Although several programmes have aimed to improve self-efficacy, most have primarily targeted psychological components [91]. To date, there is limited evidence regarding the role of exercise programmes in enhancing self-efficacy. The present study will therefore investigate whether postoperative exercise interventions can strengthen this capacity. If confirmed, these results could support a paradigm shift in which rehabilitation after colostomy is not only conceived as a way to restore mobility but also as a strategy to empower patients, improve their self-management skills, and ultimately promote autonomy and resilience in daily life.

Despite the strengths of the proposed study, several challenges may arise, particularly in patient recruitment and adherence to the intervention. Individuals living with a colostomy often experience diverse biopsychosocial impairments that could limit their participation in exercise programmes. In addition, the sample is expected to be heterogeneous, as patients undergoing this surgery vary widely in age, underlying condition, and comorbidities. This variability may influence baseline functional capacity and the magnitude of treatment effects. To mitigate these factors, the programme has been designed with individualized exercise progression and continuous monitoring, and a stratified analysis will be performed to explore potential subgroup differences.

Ensuring adherence in long-term, home-based interventions is also challenging, as motivation is strongly influenced by perceived benefits and barriers. To enhance engagement, participants will receive clear explanations of all study phases and continuous educational support. The intervention will further incorporate weekly telematic supervision, motivational reinforcement, and individualized feedback from the physiotherapist. These strategies are expected to optimize adherence, reduce dropout rates, and improve the overall feasibility and clinical applicability of the programme.

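### The hypothesis is worded for exercise patients who complete the programme, which contradicts the unconditioned aim and the abstract's intention-to-treat statement, and section 2.9 leaves the primary analysis set open

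*Protocol article*

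**What the plan says.** The article makes four statements about whom the trial compares.

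- **Hypothesis (Introduction, last paragraph).** "participants who complete the 12-week home-based gradual exercise programme will demonstrate greater improvements in physical activity levels", and in quality of life, kinesiophobia, exercise capacity and self-efficacy, "compared with those receiving standard medical care". The exercise side is limited to completers; the control side carries no condition.
- **Aim (same paragraph).** "The present study aims to evaluate the effect of a home-based gradual exercise programme on physical activity" and the other four outcomes. Completion is not mentioned.
- **Abstract.** "Data will be analyzed using intention-to-treat principles".
- **Section 2.9.** "a Mixed ANOVA with a Group (intervention vs. control) × Time (baseline, post-intervention, 6 months) interaction will be conducted for all primary outcomes". The set of patients entering this model is not named. The section then adds: "Secondary analyses will include intention-to-treat and per-protocol approaches as described above". Nothing earlier in the article describes either approach.

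On the control arm, section 2.6.2 provides usual care and a leaflet: "No supervised exercise intervention will be provided".

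**The concern.** Whether a patient completes 12 weeks of exercise is known only after randomisation, and only patients given the programme can complete it. A contrast of exercise completers with patients on standard care therefore sets a selected part of one randomised group against an unselected group. Any difference could reflect the programme, the characteristics of people able to finish it, or both.

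The article's own reasoning makes a link between completion and outcome plausible. The Introduction treats self-efficacy as a determinant of adherence and associates kinesiophobia with lower participation in other clinical populations; both are primary outcomes here. The Discussion adds: "Individuals living with a colostomy often experience diverse biopsychosocial impairments that could limit their participation in exercise programmes".

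At stake is which comparison the trial will report as its main result. The aim and the abstract point to the randomised comparison. The hypothesis points elsewhere, and the statistical section does not decide between them.

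**Working it through.** **1. The statements side by side**

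| Place | Exercise side | Condition on completion? |
|---|---|---|
| Introduction, aim | the programme in people with permanent colostomies | no |
| Introduction, hypothesis | those who complete 12 weeks | yes, this arm only |
| Abstract | intention-to-treat | no |
| Section 2.9, main model | intervention vs control | set not stated |
| Section 2.9, secondary analyses | intention-to-treat and per-protocol | neither set defined |

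The hypothesis and the aim cannot both define the question. Section 2.9 does not break the tie: if intention-to-treat is a secondary analysis, the main one is by implication something else, and the article does not say what.

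**2. An SD for scale**

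Section 2.8 gives a difference of 1,100 steps/day, α = 0.05, 80% power and 44 participants (22 per arm), but no SD, so 44 cannot be reproduced directly. Solving backwards, a two-sided two-sample t test with 22 per arm reaches 80% power at a standardised difference of 0.8646. The implied SD is 1,100 / 0.8646 ≈ 1,272 steps/day. (The normal approximation gives about 1,302, and a one-sided t test about 1,443.)

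**3. Bias if the hypothesis were tested as worded, with no true effect**

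Assume that a patient completes when a standard normal trait exceeds a cut-off c, that a share q completes, and that the trait has correlation r with the untreated outcome. Then

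bias = r × SD × φ(c) / q, with c the (1 − q) quantile of the standard normal.

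- q = 0.85: φ(c)/q = 0.274
- q = 0.70: φ(c)/q = 0.497

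For example, at q = 0.85 and r = 0.5: 0.5 × 1,272 × 0.274 ≈ 174 steps/day, and 174 / 1,100 ≈ 16%. At q = 0.70 and r = 0.5: 0.5 × 1,272 × 0.497 ≈ 316, and 316 / 1,100 ≈ 29%.

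Type I error was simulated with 10,000 runs per row, 26 vs 25 patients, and a t test of exercise completers against all controls.

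| q | r | Bias (SD) | Bias (steps/day) | Share of 1,100 | Type I error |
|---|---|---|---|---|---|
| 0.85 | 0 | 0 | 0 | 0% | 0.052 |
| 0.85 | 0.2 | 0.055 | 70 | 6% | 0.051 |
| 0.85 | 0.3 | 0.082 | 105 | 10% | 0.057 |
| 0.85 | 0.5 | 0.137 | 174 | 16% | 0.075 |
| 0.70 | 0 | 0 | 0 | 0% | 0.052 |
| 0.70 | 0.2 | 0.099 | 126 | 11% | 0.064 |
| 0.70 | 0.3 | 0.149 | 190 | 17% | 0.076 |
| 0.70 | 0.5 | 0.248 | 316 | 29% | 0.120 |

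Comparing everyone as randomised, with complete outcome data, type I error stays at 0.048–0.052 in every row.

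**4. What is assumed**

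The article gives neither r nor a completion rate. The 85% borrows the 15% dropout of section 2.8, which is an overall figure and not non-completion in the exercise arm; the 70% is a further assumption. The simulation uses a simple t test, not the mixed ANOVA.

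**The case against.** The strongest defence is that this is one loosely worded sentence. The aim is unconditioned, the abstract commits to intention-to-treat, and the model in section 2.9 compares intervention with control. Much of this stands, and it rules out several stronger readings.

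- **That the trial will compare completers with all controls.** A reader might infer this from the hypothesis, but no section plans that analysis, and the text does not say that all controls are meant.
- **That the per-protocol analysis has the same one-sided selection.** Its set is undefined. It could restrict both arms, for example by attended assessments.
- **That the Discussion says who will stop.** It says only that impairments could limit participation. It neither identifies those patients nor says they would do worse untreated. Section 2.4 also excludes several conditions that limit participation.
- **That the bias must favour the programme on all five outcomes.** The hypothesis concerns improvement and the model tests Group × Time. A stable difference in frailty is present at baseline too and largely cancels in change. The correlation with untreated change could be near zero or negative.
- **That the bias could exceed half the target.** An SD of 2,500 with r = 0.5 and 70% completion gives 0.5 × 2,500 × 0.497 ≈ 621 steps/day, or 56% of 1,100. Nothing in the article supports that SD; the one consistent with N = 44 under a two-sided t test is about 1,272.
- **That there is no reason to keep measuring patients who stop.** The three assessments are scheduled without reference to adherence.

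The defence does not remove the contradiction. The abstract would settle it if section 2.9 agreed, but section 2.9 places intention-to-treat among the secondary analyses. This is a conflict within the article, not detail left to an analysis plan.

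**Conclusion.** The point holds as an inconsistency that should be corrected. The hypothesis conditions one arm on a post-randomisation event, against the article's own aim and abstract, and section 2.9 does not restore the randomised comparison as primary. The article does not show that the trial's question as a whole, or any planned analysis, is confounded.

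The size is conditional on the hypothesis being tested as worded: 0–174 steps/day at 85% completion and 0–316 at 70%, or 0–29% of the 1,100-step target, with type I error between about 0.05 and 0.12. If completion is unrelated to the outcome, the bias is zero. These figures rest on the back-solved SD, assumed correlations of 0 to 0.5 and assumed completion rates. The direction on change scores is also an assumption.

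**What to change.** 1. **Introduction.** State the hypothesis for participants randomised to the 12-week programme, whether or not they complete it, compared with those randomised to standard care.
2. **Section 2.9.** Make the as-randomised (intention-to-treat) comparison the primary analysis, and name it as the set for the Group × Time model. State that it includes the planned 12-week and six-month assessments of patients who stop exercising.
3. **Section 2.9.** Label any completer or per-protocol result as supportive and non-randomised, and replace the reference to an earlier description that does not exist.

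The article says that no data have yet been collected, so the changes to the document are wording only. The cost is a somewhat smaller expected effect than among completers, and some effort to keep assessing patients who stop exercising at visits already planned.

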## 2. Materials and Methods

### 2.1. Design

The study is designed as a randomized clinical trial to analyze the effect of a home-based gradual exercise programme in patients with a permanent colostomy, commencing six weeks after surgery. The research assistant responsible for data collection will be blinded to the study hypothesis and patient group allocation. Due to the nature of the intervention, participant blinding will not be feasible. The study protocol will be registered at Clinicaltrials.gov: DF0103UG.

### 2.2. Ethical Considerations

The study protocol will be approved by the local Research Ethics Committee. The trial will be conducted in accordance with the 1975 Declaration of Helsinki [33], as revised in 2024, and the Consolidated Standards of Reporting Trials (CONSORT) [34]. Written informed consent will be obtained from all participants after a detailed explanation of the study procedures.

### 2.3. Setting

This study will be conducted at Virgen de las Nieves Hospital in Granada (Spain). Participants will be recruited from the general digestive surgery department.

### 2.4. Participants

Patients over 18 years of age who have undergone surgical treatment resulting in a permanent colostomy will be eligible. A colostomy is a surgical opening of the large intestine (colon) through the abdominal wall, providing a new pathway for waste elimination. A colostomy is considered permanent when restoration of intestinal continuity is not possible or not planned [1,3].

Based on a review of current literature, six weeks postoperatively is considered an appropriate timeframe for patients to adjust to their new condition and home environment, making this period suitable for initiating a home-based exercise intervention [4].

Exclusion criteria will include the following: pulmonary, cardiac, neurological, vascular, or orthopedic conditions limiting participation; cognitive impairment preventing comprehension of the intervention; ostomy-related complications; and refusal to provide informed consent.

### 2.5. Randomization

Eligibility will be assessed by an impartial professional uninvolved in the randomization process. Randomization will be performed by an independent researcher who will not participate in patient assessment or treatment. Patients will be assigned sequentially to groups using a computer-generated randomization sequence (https://www.randomizer.org) with a 1:1 allocation ratio. The randomization sequence will be securely maintained off-site. Group allocation will be communicated to the recruiter via email, and assessments will be carried out by a physiotherapist blinded to group allocation.

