#### 2.7.2. Covariables

Anthropometric data such as age, gender, and body mass index, and clinical data such as personal medical history, indication for surgery, regular medication use and comorbidities assessed with the Charlson Comorbidity Index will be recorded [37].

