### 2.8. Sample Size Calculation

An a priori sample size calculation was based on the minimum clinically important difference (MCID) of the physical activity level interference estimated to be 1100 daily steps [57]. Using G*Power version 3.1.9.2, we obtained a sample size of 44 participants, equally distributed between the treatment and control groups, based on a confidence level of 95% (α = 0.05) and a power of 80% (β = 0.2). Anticipating a 15% dropout rate, the total sample size was increased to ensure adequate statistical power, resulting in a sample size of 51 participants.

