## 4. Discussion

This study is expected to demonstrate the effectiveness of the intervention in enhancing physical activity and quality of life compared with the control group, while also reducing kinesiophobia and improving exercise capacity and self-efficacy. The results of this study are expected to demonstrate the effectiveness of the intervention in enhancing physical activity and quality of life compared with the control group. Moreover, the programme is expected to reduce kinesiophobia and enhance both exercise capacity and self-efficacy. Through this study, the authors aim to provide clinicians with an evidence-based intervention capable of addressing both the physical and psychological challenges inherent to postoperative recovery.

The study sample is expected to be heterogeneous, as permanent colostomy is performed for a range of underlying conditions. Considerable variability is also anticipated in anthropometric characteristics. For instance, patients with Crohn’s disease who undergo permanent colostomy typically receive this treatment in the third or fourth decade of life [58], whereas those with colorectal cancer generally undergo surgery between 65 and 70 years of age [59,60,61]. Sex-specific variability is also expected: colorectal cancer is more prevalent among men [59,62], while colostomies performed for conditions such as diverticulitis are more common among women [63,64]. This heterogeneity will need to be considered when interpreting the results, as baseline differences in functional capacity, lifestyle habits, and comorbidities may influence the magnitude of the intervention’s effects. A carefully planned randomization process should help balance these factors between groups, but subgroup analyses may also be required to better understand whether certain patient profiles will benefit more from the programme than others.

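### The article expects a mixed sample and leans on randomisation to balance it, yet describes no stratification and fixes a Group × Time mixed ANOVA that uses neither its listed covariables nor baseline as a covariate, giving up precision at no gain

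*Protocol article*

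**What the plan says.** Section 2.5 (Randomization): "Patients will be assigned sequentially to groups using a computer-generated randomization sequence", "with a 1:1 allocation ratio". The section names the tool, off-site custody of the list and the email route for allocations. It mentions no stratification factor, block or minimisation.

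Section 4 (Discussion) expects a heterogeneous sample: different indications, with quite different typical ages at surgery. It allows that baseline differences may influence the size of the effect, and then says: "A carefully planned randomization process should help balance these factors between groups". It adds that subgroup analyses may be needed, and later that "a stratified analysis will be performed to explore potential subgroup differences". No stratifying factor is named.

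Section 2.7.2 (Covariables) lists "Anthropometric data such as age, gender, and body mass index, and clinical data such as personal medical history, indication for surgery", along with regular medication and the Charlson Comorbidity Index.

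Section 2.9 (Statistical Analysis) fixes the model for all primary outcomes: a mixed ANOVA with group and three time points, baseline being one of them. It has no covariate or stratum term and does not mention the stratified analysis.

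Section 2.8: "we obtained a sample size of 44 participants, equally distributed between the treatment and control groups", then a 15% dropout allowance, "resulting in a sample size of 51 participants".

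**The concern.** These sections do not fit together. The Discussion treats indication, age and comorbidity as likely to matter and looks to randomisation to even them out. The allocation method as described does nothing specific for those factors, and at about 25 patients per arm chance alone can leave a visible gap in a common one. The variables are collected and called covariables, yet have no role in the stated model. The one analysis that would use such factors is exploratory, appears only in the Discussion and does not adjust the main comparison.

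The stakes are precision and credibility. A small trial can least afford to leave explainable variation in its error term. An imbalance in indication would also invite doubt about the result, with no prespecified adjusted estimate to answer it.

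**Working it through.** **The plan's own figure.** 44 × 1.15 = 50.6, rounded up to 51, so the stated 51 reproduces. (Dividing instead, 44/0.85 = 51.8, gives 52; the difference does not matter here.) The base of 44 cannot be rebuilt, because the article gives 1100 steps/day but no SD. Back-solving a two-sided t test with 22 per arm, α = 0.05 and 80% power gives a standardised effect of 0.865, so SD ≈ 1100/0.865 ≈ 1272 steps. A one-sided test would give about 1443.

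**Chance imbalance in one binary factor.** Inputs: N = 51 (section 2.8) and 1:1 allocation (section 2.5). Assumptions not in the article: simple randomisation, the prevalence of the factor, and a 20-point gap as the threshold. With K of the 51 patients carrying the factor, each patient goes to either arm with probability 0.5. Sum the probabilities of all outcomes in which the arm proportions differ by at least 0.20:

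| Prevalence | Simple randomisation | Fixed arms of 25 and 26 (hypergeometric) |
|---|---|---|
| 50% | 16.2% | 16.5% |
| 40% or 60% | 15.8% | 15.3% |
| 30% or 70% | 12.9% | 13.2% |
| 20% or 80% | 7.0% | 7.5% |
| 10% | 1.5% | 2.3% |

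The result is about 13–16% at 30–70% prevalence and about 2–7% at 10–20%. It depends on the threshold. For prevalence 20–80% with fixed arms, a 15-point gap has probability 17–27%, a 25-point gap 1–10% and a 30-point gap 1–3%.

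**How far such a gap could move the steps comparison.** Shift = 0.20 × D, where D is the difference in steps/day between the two categories. Assume the factor explains 20% of the variance, so p(1 − p)D² = 0.20 × SD². With SD = 1272:

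- p = 0.5: D = 1272 × √(0.20/0.25) ≈ 1138; shift ≈ 228 steps, 21% of 1100.
- p = 0.3: D = 1272 × √(0.20/0.21) ≈ 1241; shift ≈ 248 steps, 23% of 1100.

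This applies to a comparison of levels. The Group × Time test cancels stable level differences, so only an effect of the factor on change would remain.

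**Value of baseline adjustment.** Let σ² be the outcome variance, equal at baseline and follow-up, and ρ their correlation (both assumptions). Per patient, the variance of change from baseline is 2σ²(1 − ρ), and the residual variance after baseline adjustment is σ²(1 − ρ²). The ratio is (1 + ρ)/2.

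| ρ | Change: 2(1 − ρ) | Adjusted: 1 − ρ² | Reduction |
|---|---|---|---|
| 0.3 | 1.40 | 0.91 | 35% |
| 0.5 | 1.00 | 0.75 | 25% |
| 0.7 | 0.60 | 0.51 | 15% |

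This compares the two approaches at a single follow-up visit. The mixed ANOVA's interaction over three time points is a broader test, but its contrasts with baseline are change contrasts.

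**The case against.** The strongest reply has four parts.

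- *Valid randomisation needs no help.* Chance imbalance does not bias the test or inflate type I error. This stands, and the point is therefore one of precision and credibility.
- *The model already deals with baseline.* With baseline as a time level, Group × Time tests change, and stable differences linked to indication or age drop out. This also stands. A reader might infer that nothing in the analysis corrects an imbalance, which would be wrong. What is left is any effect of these factors on change, and the inefficiency of a change comparison against baseline adjustment.
- *The harm is small.* A reader might infer that imbalance could move the steps comparison by as much as the effect sought. With a 20-point gap that would require the categories to differ by 1100/0.20 = 5500 steps/day, about 4.3 SD at SD 1272. Nothing in the article supports that. A reader might also credit adjustment for indication and age with a 25% gain in sample size, from 1/(1 − 0.20). That formula assumes the explained variance sits in the error term of the test, and stable between-patient variance does not enter the Group × Time error term.
- *The article is condensed.* Blocks and strata may be set out in the full protocol, and the Discussion says only that randomisation should help. This is fair. Silence in section 2.5 is weak ground by itself, and it does not establish that the list is unblocked.

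The last reply does not reach section 2.9. There the model is stated explicitly, and it leaves out variables that the article itself labels covariables.

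**Conclusion.** The point holds as a moderate design weakness. The firm part is the mismatch between the Discussion (heterogeneity, reliance on balance, a stratified analysis) together with section 2.7.2, and sections 2.5 and 2.9, where no stratification is described and no covariate is used. The validity of the test is not in question.

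The imbalance probabilities are conditional on simple randomisation, a 20-point threshold and an assumed prevalence. The article gives no prevalence for any indication, so no single probability should be quoted as a property of this trial. The better-supported gain is the 15–35% cut in variance from baseline adjustment, which rests on an assumed correlation of 0.7 to 0.3 and equal variances over time. Any extra gain from age and indication depends on how strongly they predict follow-up given baseline, which the article does not allow one to estimate.

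**What to change.** **Main change, section 2.9.** Replace the mixed ANOVA with a model of the post-intervention and 6-month values (a repeated-measures mixed model, or ANCOVA at each visit). Include group, time and group × time, adjusted for the baseline value of the outcome, age and indication (malignant v non-malignant). This is a change of model: baseline cannot remain a level of the time factor and also be added as a covariate. All the variables are already collected. The cost is rewriting the analysis paragraph and a few degrees of freedom.

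**Supporting change, section 2.5.** Generate the list in random permuted blocks, stratified by indication only, held by the independent researcher as already planned. The Data Availability statement says no data have yet been collected, so the list can still be changed. The downside is one extra item, the indication, with each allocation request. If the full protocol already specifies blocks or strata, stating them here is enough.

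**Section 4 and section 2.9.** Name one group × indication interaction, labelled exploratory, in place of the stratified analysis with unnamed factors. It will be weak. With 44 patients split evenly (11 per cell) and an interaction as large as the main effect (0.864 SD), the noncentrality is 0.5 × 0.864 × √11 ≈ 1.43, and on 40 df power is about 29%. It should be reported as an estimate with its interval.
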